**IX-2. Methods and schedule for measuring, collecting and analysing these parameters (details in appendix)**

**IX-2-1. Intensity of an AE**

It will be evaluated as follows:

- Mild : minimal inconvenience without affecting everyday activities;
- Moderate: Sufficient inconvenience to affect daily activities;
- Severe: Inability to perform daily activities;
- Death

**IX-2-2. Causal relationship between AEs and the study procedures**

**IX-3. Procedures for Adverse Events**

**IX-4. Data Safety and Monitoring Board**

The Data Safety and Monitoring Board (DSMB) is an advisory committee responsible for advising the Sponsor on the benefit / risk ratio and the conduct of a clinical trial.

The role, composition and functioning of the DSMB are detailed in the DSMB operating charter.

**IX-5. Methods and duration of follow-up following the occurrence of an adverse event (details in appendix)**

**X. STATISTICAL METHODS**

**X-1. Analysis populations**

**X-1-1. Flow diagram**

At the final analysis of trial, a flow chart will be constructed according to the CONSORT 2010 reporting guidelines. It will describe:

- The number of eligible patients, randomized patients and the number of patients who have actually followed the study;
- The intervention arm allocated per randomisation;
- Early cessation of the intervention and their causes and drop-outs;
- The number of patients excluded from the analysis.
- The number of randomized but ineligible patients, if any, will also be reported, as well as the reason for ineligibility.

**X-1-2. Intention to treat population**

The analyses will be performed according to the intention-to-treat (ITT) principle. The ITT population (by patient cohort) will be used for all efficacy analyses. This will consist of all randomised patients according to their allocated arm irrespective of whether the patient actually received study drug or the patient's compliance with the study protocol, in the treatment group assigned by the randomization.

The list of protocol deviations will be established and the reasons for non-evaluable cases will be indicated as following:

- Inclusion criteria not satisfied.
- Deviations related to the study drug administration

All randomized patients will be included in the primary ITT efficacy analysis.

A modified intention to treat population (mITT) will be considered. The modified ITT population will exclude ineligible patients who were randomized in error.

### **X-1-3. Safety analysis population**

All patients who received convalescent plasma will be included in the Safety analyses.

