**Safety:**

13. Number of serious Adverse Events at 72 hours after randomisation (Grade 3/4 adverse events and AE unexpected for their nature, onset, evolution, severity or frequency)
14. Arterial and venous thromboembolic events at 28, 90 and 180 days after randomization

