## **IV. STUDY DESIGN**

### **IV-1. Overall design**

COVIC-19 is a multicentre international, randomised, open-label adaptive superiority phase III trial to evaluate the efficacy and safety of COVID-19 convalescent plasma in the treatment of COVID-19. It is conducted in a harmonized approach in different countries in Europe.

The study is randomizing adult COVID-19 patients to one of two arms (1:1 ratio): standard of care or standard of care and very high neutralizing Ab titre convalescent plasma. Randomization will be stratified by centre and by patient cohort. The control group will receive 'standard care' therapy. Neither blinding nor placebo will be used to avoid unnecessary intravenous access.

Standard of care therapy may include anti-SARS-CoV-2 specific medication listed as authorized in a dedicated appendix. Centres should ensure that medications used as standard of care are used similarly for patients in both treatment arms.

Participating patients will be included in 2 cohorts of vulnerable patients (cohort 1: unvaccinated elderly ( $\geq 70$  years) and younger with comorbidities (cohort 1:  $< 70$  with comorbidities), cohort 2: immunosuppressed patients).

All subjects will undergo a series of efficacy and safety assessments, including laboratory assays. Subjects will be assessed at baseline, and at Days 3, 14, 28, 90 and 180.

Nasopharyngeal swabs (NP) or lower respiratory tract samples will be obtained at D1 (pre-treatment), and at D3, D14, D28 and D180 (and monthly in case of positivity until of clearance) for cohort 2 and on the day of hospitalization (if applicable).

Blood samples will be obtained at D1, D14 and D28 and on the day of hospitalization (if applicable).

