| CCP administration (only in
treatment arm)        |                                             | X              |                |                |                |                                                        |             |                |
| Study procedures                              |                                             |                |                |                |                |                                                        |             |                |
| Demographics and Medical History                     | X                                           |                |                |                |                |                                                        |             |                |
| Examination / Vital signs                            |                                             | X              |                |                |                | X                                                      |             |                |
| Symptom recording                                    | X                                           | X              | X              | X              | X              | X                                                      |             |                |
| Vital status                                         |                                             | X              |                |                | X              | X                                                      | X           | X              |
| Concomitant medications                              | X                                           | X              | X              | X              | X              | X                                                      |             |                |
| Hospitalisation/ITU                                  |                                             | X              | X              | X              | X              | X                                                      |             |                |
| Ventilation mode                                     |                                             |                |                | X              | X              | X                                                      |             |                |

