| SARS CoV 2 antibody in serum                                                    | X              | X                | X  | X  | X    | X                |  |                  |
| Biochemistry bloods                                                 |                | X                |                | X  |                  | X                |  |                  |
| Haematology bloods                                                  |                | X                |                | X  |                  | X                |  |                  |
| Pregnancy test (in females of childbearing potential only)                      | X              |                  |                |                |                  |                  |  |                  |
| Serum for biobank (optional)                                                    |                | X    |                | X  | X    | X    |  |                  |
| Plasma for biobank (optional)                                                   |                | X    |                | X  | X    | X    |  |                  |
| EDTA sample (for isolation of immune cells) for biobank (optional)              |                | X    |                | X  | X    | X    |  |                  |

 For individuals with no RT PCR or Antigenic test result in the preceding 7 days

 Cohort 2; in cohort 1 only if the patient's have not been tested negative in the SARS-CoV-2 PCR before.

 Urea, Electrolytes, Liver Function Tests (ALT, AST), Creatinine, calcium, phosphate, glucose, C-reactive protein (CRP). LDH, ferritin, IL-6 (optional)

 Full Blood Count (neutrophils/total lymphocyte counts, platelets), Prothrombin, Activated partial thromboplastin time (aPTT), fibrinogen, D dimer, G&S

 Visit "hospitalization" on the day of hospitalization and/or start of supplementary O2 (+ 2 days) (only if this event occurs up to day +28).

 if viral load still sufficient to perform sequencing or virus isolation

 between screening and administration of CCP (D1)

 not mandatory

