### **Safety analysis of intervention**

Safety endpoints include the following:

- Number of serious Adverse Events at 72 hours after randomisation (Grade 3/4 adverse events and AE unexpected for their nature, onset, evolution, severity or frequency)
- Arterial and venous thromboembolic events at 28, 90 and 180 days after randomization

Adverse events and their characteristics will be described using numbers and percentages per treatment arm. The proportion of participants with each of the reported events, as well as the

proportions of participants with at least one SAE will be compared using Fisher's exact tests. The total number of AE/SAEs and SAEs will also be described for each arm, and compared using Poisson models (with a robust error variance if necessary).

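### The safety population is defined as plasma recipients only, which contradicts the between-arm safety comparisons planned in X-3

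*Protocol*

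**What the plan says.** The whole of X-1-3 (Safety analysis population) reads: "All patients who received convalescent plasma will be included in the Safety analyses". Control patients are not mentioned there, and no other section adds them to the safety set. X-1-2 assigns the intention-to-treat population to the efficacy analyses.

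Table 3 restricts plasma administration to the treatment arm. IV-1 says of the controls: "The control group will receive 'standard care' therapy. Neither blinding nor placebo will be used to avoid unnecessary intravenous access".

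The safety part of X-3 is written for two arms. It states: "Adverse events and their characteristics will be described using numbers and percentages per treatment arm". It adds that the proportions with each reported event are to be compared, and likewise that the "proportions of participants with at least one SAE will be compared using Fisher's exact tests". Total event counts are also to be described for each arm and compared with Poisson models.

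The first safety endpoint in III-4 is "Number of serious Adverse Events at 72 hours after randomisation"; the second is thromboembolic events at 28, 90 and 180 days. Footnote 7 of Table 3 places randomisation between screening and the administration of plasma on D1. VII-1 puts the first unit on day 1 and the second on day 1 or day 2.

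**The concern.** A between-arm test needs patients in both arms. Under X-1-3 the only patients outside the plasma arm who could enter the safety set are controls who happened to be given plasma, and they are not a control group.

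The controls matter because the disease itself produces the events being counted. Under IX-1-2, death and in-patient hospitalisation are serious adverse events, and IX-1-1 lists hospitalisation and death from progressive COVID-19 as expected ones. A rate seen in plasma recipients alone cannot separate harm from plasma from the course of COVID-19. The same holds for thromboembolic events. Safety is a stated secondary objective (III-2), so the population on which it is judged should be one in which the planned tests can be run.

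A smaller question concerns the 72-hour endpoint. Its clock starts at randomisation and not at exposure, so the observed period may not always cover the transfusions.

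**Working it through.** **1. Arm sizes.** Inputs from X-2: 0.30 in controls, 0.15 with plasma, two-sided alpha 0.05, power 90%, Z-test. With unpooled variance:

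n = (0.30 × 0.70 + 0.15 × 0.85) × (1.960 + 1.282)² / 0.15² = 0.3375 × 10.51 / 0.0225 ≈ 157.6, rounded up to 158 per group.

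This reproduces the protocol's figure (power at 158 is 0.901). X-2 then raises the group size to 170, which gives 2 × 170 = 340 per cohort and 680 in all. The sample size is not in dispute; it only fixes the denominators.

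**2. Who is in the safety set** (per cohort, stage 1, full adherence, no crossover):

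| Definition | Plasma | Control |
|---|---|---|
| X-1-3 as written | about 170 | 0 |
| All randomised, by treatment received | about 170 | about 170 |

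At the maximum of 1020 per cohort, the arm left out would be 1020 / 2 = 510.

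**3. What the planned tests return with an empty control row.** Fisher's exact test on 5 events in 170 against 0 in 0 gives an undefined odds ratio and p = 1.0. With 17 in 170 against 0 in 0 the result is the same. The p-value does not depend on the number of events. A Poisson rate ratio between arms cannot be estimated without control patients.

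**4. Why an uncontrolled rate would not help.** On the X-2 assumptions, disease progression alone would affect about 0.15 × 170 = 25.5 plasma patients and 0.30 × 170 = 51 controls by day 28. X-2 states these rates for severe COVID-19, so they only approximate the rate of hospitalisation or death.

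**5. The 72-hour clock.** The second unit is taken as given about 24 hours after the first.
- Randomised on D1: the second unit falls 24 hours into the window, leaving 72 − 24 = 48 hours after it.
- Randomised two days before D1: the second unit falls at 48 + 24 = 72 hours, just as the window closes.
- Randomised three days before D1: the window closes at about the time of the first unit.

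The delays in the last two cases are illustrations. The protocol gives no distribution of the time from randomisation to infusion.

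**The case against.** The strongest reply is that X-1-3 says that all plasma recipients are included, not that only they are, and that X-3 leaves no doubt that the arms are to be compared. Table 3 records adverse events from D1 to D180 without restriction by arm, and VI-4-2 requires follow-up of every participant. No analyst would run a Fisher test on an empty row. Hospitalisation and death, the expected serious events, are in any case compared by arm as efficacy endpoints. X-3 also promises a more detailed statistical analysis plan.

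Much of this stands. A reader might infer that no comparative safety conclusion will be possible, or that control data will be lost. The protocol does not support that: the intent is explicit and the data are collected. What does not fall away is the contradiction. X-1-3 is the complete definition under its heading, and the population that does contain the controls is assigned to efficacy. An analysis plan would have to depart from X-1-3 or from X-3, and in an open-label trial that choice should be settled before outcomes accumulate.

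On the 72-hour endpoint, a reader might infer that transfusion reactions will be under-counted in general. That is not supported either. Table 3 marks randomisation in the D1 column, VII-1 asks for prompt infusion once a patient is randomised, and eligibility requires that transfusion be possible within 7 days of symptom onset. Total events are also compared in X-3 without a stated 72-hour limit, and VII-4 requires suspected serious transfusion reactions to be reported. Randomisation is a defensible common origin, since controls have no infusion to start a clock. What remains is a bounded possibility affecting one endpoint in patients transfused late.

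**Conclusion.** X-1-3 is wrong as written. It leaves the standard-of-care arm, about 170 of 340 patients per cohort at stage 1, out of the set in which X-3 plans per-arm description, Fisher's exact tests and Poisson comparisons, and those comparisons cannot be made in that set. The figure assumes 1:1 allocation at the planned size, full adherence and no crossover. This is an error of definition with a clear intended meaning. It does not affect the sample size, the efficacy analyses or the data collected.

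The 72-hour window is a minor point. Footnote 7 permits randomisation before D1, so the window can close before or soon after exposure is complete, but how often this would happen is unknown and the instruction in VII-1 limits it.

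**What to change.** Redefine the safety population in X-1-3 as all randomised patients, grouped by treatment actually received: any volume of convalescent plasma versus none. State that a control patient who was given plasma counts in the plasma group, and that a plasma-arm patient who was never transfused counts in the group without plasma. Because some of the latter may have worsened before infusion, repeat the safety analysis as randomised, so that their placement does not distort the comparison unseen.

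If the 72-hour endpoint is also addressed, use a window of equal length in both arms, for example D1 to D5, and define D1 for controls, since footnote 7 ties it to plasma administration. A second unit about 24 hours after the first, followed by 72 hours, ends 96 hours after D1, which is D5, and the D3 visit with its +2-day allowance already reaches that day. Do not extend the window in the plasma group only: that would set 96 hours of observation against 72 and bias the comparison against plasma.

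The cost is protocol and analysis plan wording. No new visits or data items are needed.

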### **X-2. Sample size determination**

The Sample size of the study is based on the risk of severe COVID-19 and the effect previously observed by Libster et al. in an elderly high-risk population and a similar intervention of early convalescent plasma. In this study, 31% of the control group patients experienced severe COVID-19 disease, the relative risk of severe COVID-19 in treated patients was 0.52 (95% Confidence Interval 0.29–0.94). We estimate that the risk of severe COVID-19 in the elderly population will be 30% and the relative risk reduction in the treated group will be 0,5.

For a cohort, group sample sizes of 158 in group 1 and 158 in group 2 achieve 90% power to detect a difference between the group proportions of -0.15. The proportion in group 1 (the treatment group) is assumed to be 0,30 under the null hypothesis and 0.15 under the alternative hypothesis. The proportion in group 2 (the control group) is 0.30. The test statistic used is the two-sided Z-Test. The significance level of the test is 0.05. The sample size is increased to 170 to account for missing data/loss to follow up.

### **Interim analysis and sample size reestimation**

The SARS-CoV-2 pandemic is a constantly evolving situation and with the appearance of new variants, there is considerable uncertainty as to the real risk of severe COVID-19 in the population. There is little data regarding the risk of severe COVID-19 in the immunocompromised population. Moreover, the effect observed by Libster et al. may be overly optimistic by chance and may be different in our trial because of local variations in donor selection and plasma production methods. If the effect is overestimated, the trial may not achieve the desired power. Thus, we will include a sample size reestimation during the course of the trial as a form of adaptive design.

For each cohort, sample size re-estimation will be planned using the method proposed by Mehta and Pocock. Specifically, for each cohort, an interim analysis will be conducted when 30% of the patients, have reached the primary endpoint assessment. The conditional power for detecting the difference in primary outcome between the two arms in the final analysis will then be estimated. If the conditional power is between 50% and 90%, the sample size will be increased in order to achieve 90% power to detect the effect observed at the interim analysis with a maximum sample size of 1020 per cohort. Otherwise, the trial will continue using the planned sample size.

The table below presents the conditional power and estimated effect at interim analysis for values of Z1 between which sample size will be increased.

| Z at interim analysis | Conditional power | Estimated effect at interim analysis (risk difference) | Estimated effect at interim analysis (relative risk) |
|------------------------------|--------------------------|---------------------------------------------------------------|-------------------------------------------------------------|
| 1.07                         | 0.50                     | -0.09                                                         | 0.66                                                        |
| 1.66                         | 0.90                     | -0.14                                                         | 0.52                                                        |

The interim analysis will be performed by an independent statistician and presented to the DSMB. Decision boundaries are non-binding, and the DSMB can recommend continuing the trial at the pre-planned sample size.

Sample size reestimation boundaries and the size of the sample size increase were produced using the gsDesign package v. 3.2 (K. Anderson, Merck research laboratories, Boston, MA) with R version 4.0.5 (The R Foundation for Statistical Computing, Vienna, Austria).

### **X-3. Statistical analysis**

#### **General principles**

All analyses for reports, presentations and publications will be prepared by the coordinating centre at the Research Methods Unit (uMETH) of the Clinical Investigation Centre, University Hospital of Besançon. A more detailed statistical analysis plan will be developed by the investigators whilst still blind to any analyses of aggregated data on study outcomes by treatment allocation.

Although conducted as a single trial with randomisation stratified on the groups of patients (cohort 1 and 2) for operational and logistical reasons, the findings in each cohort are considered as separate trials and are analysed separately.

The final results will be reported according to the recommendations of CONSORT 2010.

All outcomes will be analysed in superiority (two-sided) analyses using simple hypothesis tests. As sensitivity analyses, generalized linear models will be used to account for stratification on the centre. No correction for multiplicity and no hierarchical testing procedures are planned in analysing secondary outcomes. These analyses will therefore be considered as exploratory in nature.

#### **Handling of missing or incoherent data**

In the case outcomes would be missing, binary missing outcomes will be treated as treatment failures in interim and primary final analyses, with an imputation by last value carried forward as a sensitivity analysis. For time-to-event outcomes, they will be naturally handled using methods for censored data. No imputation will be used for secondary efficacy and safety outcomes.

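### The increase from 158 to 170 per arm assumes missing patients leave the analysis, but the primary rule counts them as events, so power at the stated 5% allowance is about 85-86%, not 90%.

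*Protocol*

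**What the plan says.** Protocol X-2 states that "group sample sizes of 158 in group 1 and 158 in group 2 achieve 90% power". The control risk is fixed by "The proportion in group 2 (the control group) is 0.30", and the treated-arm risk is "assumed to be 0,30 under the null hypothesis and 0.15 under the alternative hypothesis". The test is specified by "The test statistic used is the two-sided Z-Test" and "The significance level of the test is 0.05". The section then adds: "The sample size is increased to 170 to account for missing data/loss to follow up". Sections I and IV-2 describe the same allowance as 5% additional patients, for 340 per cohort.

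X-1-2 places all randomised patients in the primary intention-to-treat analysis. Under the missing-data heading of X-3, repeated in X-6, "binary missing outcomes will be treated as treatment failures in interim and primary final analyses". The one missing-data sensitivity analysis named is last value carried forward.

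IV-1 makes the trial open-label: "Neither blinding nor placebo will be used to avoid unnecessary intravenous access". X-2 also provides for an interim re-estimation in each cohort at 30% information. It raises the sample size, up to 1020 per cohort, when conditional power lies between 50% and 90%.

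**The concern.** The two parts of the plan treat a missing patient differently. The sample size section treats missingness as lost numbers: recruit 170 and keep about 158 evaluable. The analysis section loses no numbers. It keeps the patient and assigns an event. The planning risks of 30% and 15% contain no imputed events, so the power statement does not describe the analysis that will be run.

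Two things are at stake. The first is power, because assigning events at the same rate in both arms dilutes the difference. The second is the direction of bias. With failure imputation in both arms, the arm that loses more patients is penalised. Patients know their allocation, so loss could differ by arm, and the rule would turn that imbalance into an apparent treatment effect.

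**Working it through.** **Inputs.** From X-2: two-sided alpha 0.05, control risk 0.30, treated risk 0.15, 158 per arm raised to 170. From VIII-1: 1:1 allocation. From sections I and IV-2: 5% additional patients. From X-1-2, X-3 and X-6: all randomised patients analysed, missing counted as an event.

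**Step 1: reproduce the plan's figure.** Unpooled Z-test:
n = (1.960 + 1.282)² × (0.30×0.70 + 0.15×0.85) / 0.15² = 157.6, so 158 per arm. This matches exactly. The pooled-variance version gives 161.

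**Step 2: what the 170 assumes.** Two readings reach 170: 161/0.95 ≈ 170 (5% loss), or 158 evaluable out of 170, which is 12/170 = 7.1% loss. Both remove missing patients from the analysis. On that basis the plan is sound: evaluable-patient power is 90.1-90.7% at 5% missing and 89.5-90.1% at 7.1% (pooled-unpooled).

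**Step 3: apply the rule as written.** Let m be the missing share, equal in both arms and unrelated to outcome. Then
- control: 0.30 + 0.70m
- plasma: 0.15 + 0.85m
- difference: 0.15(1 − m), with all 170 per arm analysed.

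For m = 0.05 the risks are 0.335 and 0.1925, and the difference is 0.1425. The standard error is √[(0.335×0.665 + 0.1925×0.8075)/170] = 0.0472, so the ratio is 3.02 and power is Φ(3.02 − 1.96) = 85.6%.

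| Missing, both arms | Control vs plasma | Power at 170 per arm (pooled / unpooled) |
|---|---|---|
| 1% | 30.7% vs 15.9% | 90.3% / 90.8% |
| 2% | 31.4% vs 16.7% | 89.1% / 89.6% |
| 5% | 33.5% vs 19.3% | 85.0% / 85.6% |
| 7.1% | 34.9% vs 21.0% | 82.0% / 82.6% |

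For scale, 90% power under this rule would take 196-199 per arm at 5% missing, or 213-216 at 7.1%.

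**Step 4: allow for the re-estimation.** This was simulated with the interim at 51 per arm (30% of 170), conditional power under the current trend, an increase when it lies between 50% and 90%, and a cap of 510 per arm. The same conditional power formula reproduces the X-2 table: Z of 1.07 and 1.66 give 0.50 and 0.90. With missing counted as failure, overall power is about 88% at 5% missing and about 85% at 7.1%.

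**Step 5: unequal loss, no true effect.** The arm-specific rates here are assumptions, because the protocol gives none. Take true risk 30% in both arms, with 8% missing in control and 2% in plasma:
- control: 0.30 + 0.70×0.08 = 0.356
- plasma: 0.30 + 0.70×0.02 = 0.314
- spurious difference: 4.2 points in favour of plasma.

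At 170 per arm the chance of a significant result favouring plasma is about 13%, against a nominal 2.5%. At an assumed 7% versus 3% it is 7.9%. At 5% in both arms it is exactly the nominal 2.5%.

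**Step 6: what last value carried forward does in that scenario.** If lost patients were event-free at last contact, they become non-events: 0.30×0.92 = 27.6% control against 0.30×0.98 = 29.4% plasma. The apparent benefit reverses. In simulation the primary and sensitivity analyses both significantly favour plasma only about 1% of the time.

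**The case against.** **The allowance is a contingency, not a forecast.** VI-4-2 requires follow-up of every participant through medical notes, routine healthcare systems and registries. VII-9 says that stopping treatment is not withdrawal from follow-up. The endpoint is hospitalisation or death at 28 days, which such sources can often settle. This stands in part: at 1-2% missing, power is about 89-91% and the issue is negligible. Power also falls less if the missing patients truly had events. But the plan budgets for 5% and claims 90% with that budget in place.

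**The 7.1% is back-calculated.** This stands. The only percentage the protocol names is 5%, so 85-86% is the figure to lead with, and 82-83% belongs to an alternative reading of the increase.

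**The adaptive design recovers power.** It does so in part, to about 88%. It acts only in the promising zone, X-2 makes the boundaries non-binding, and the interim uses the same diluted comparison.

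**A reader might infer that the rule will manufacture a benefit for plasma.** The documents do not support that. Nothing in them shows that controls will be lost more often. Equal loss leaves the type I error intact, and greater loss in the plasma arm biases against plasma. The point is a vulnerability and no more.

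**A reader might also infer that last value carried forward is no safeguard.** That goes too far. It sits near the opposite extreme, and Step 6 shows it would help expose the artefact. It would not, however, change the primary decision.

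**Further sensitivity analyses may be in the statistical analysis plan.** They may, and the absence of a tipping-point analysis from the protocol is not itself a fault. The power statement and the primary missing-data rule are both in the protocol, and they do not agree.

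**Conclusion.** The point holds as a mismatch between the sample size increase and the primary missing-data rule. At the protocol's named 5% allowance, fixed-sample power is about 85-86% rather than 90%, a shortfall of 4-5 points; on the 12/170 reading it is 82-83%. Re-estimation, if applied, brings these to about 88% and 85%. These figures assume missingness that is equal between arms and unrelated to outcome, together with the planning risks of 30% and 15%.

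The bias toward plasma is conditional on more missing outcomes among controls. The 13% false-claim figure illustrates assumed rates of 8% and 2% and is not a prediction. The matter should be fixed, but it does not invalidate the design.

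**What to change.** Choose one of two routes, before any unblinded data are seen.

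1. **Keep missing-as-failure as primary** and restate the power in X-2 under that rule: about 85-86% at 5% missing, 82-83% at 7.1%.
2. **Change the primary rule**, at both interim and final analyses, to multiple imputation by arm from baseline and follow-up data, used only after day-28 status has been sought through the VI-4-2 record and registry sources. Keep missing-as-failure as a sensitivity analysis, and add a tipping-point analysis that varies the event risk of missing patients separately by arm. The 170 per arm then fits the analysis approximately as X-2 intended. Multiple imputation rests on its own untestable missing-at-random assumption, which is why the tipping-point analysis belongs beside it.

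Under either route, state the assumed missing percentage once and use it consistently in sections I, IV-2 and X-2. The cost is protocol and analysis plan wording plus modest extra analysis, with no additional patients or data. Under the first route the stated power becomes less favourable.
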